**Fig. 1 Fig1:**
[figure not shown]
Overview of data collection in the DACOLT study, the Copenhagen General Population Study (CGPS) and the Copenhagen City Heart Study (CCHS). *CT* computed tomography, *FRAX®* Fracture Risk Assessment Tool

### Participants

#### DACOLT participants and eligibility criteria

All liver transplant recipient in Denmark aged 18–100 years will be eligible for inclusion in the DACOLT study. Inclusion requires the individual to be able to understand the study information in either Danish or English and to be able to provide an informed consent. Contraindications to the various measures performed in the study (i.e., renal impairment and contraindications to a contrast enhanced CT) do not exclude participants from other parts of the study.

#### Controls from the Copenhagen General Population Study and the Copenhagen City Heart Study

CGPS is an ongoing observational population study with more than 110,000 participants from the greater Copenhagen area. All residents in the greater Copenhagen area > 40 years and 25% of 20–40 years old are invited to participate in the study and in follow-up examinations every decade. A random sample of 10,000 participants aged ≥ 40 years had a contrast enhanced CT of the chest including CT angiography of the heart performed. Of these, 6500 had a contrast enhanced CT of the abdomen.

CCHS includes a random population sample included from the greater Copenhagen area. Health surveys have been repeated 5 times between 1976 and 2015. Almost 4500 participants were randomly selected for echocardiography in 2013–2015.

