## Study objectives

The overall objective of this study is to determine the burden of comorbidities in liver transplant recipients and to examine whether this differs from the background population. Furthermore, we want to identify both liver- and transplant-related risk factors as well as traditional risk factors that contribute to the pathogenesis of comorbidity in liver transplant recipients.AIM 1: To determine the prevalence and incidence of cardiovascular, respiratory, renal and metabolic diseases in liver transplant recipients, and whether the prevalence and incidence of these comorbidities are different from that of the background population.AIM 2: To identify liver- and transplant-related risk factors and traditional risk factors that contribute to the pathogenesis of cardiovascular, respiratory, renal and metabolic diseases in liver transplanted recipients and study potential interactions between these.AIM 3: To describe the kinetics of cytokines, chemokines, immune cells, proteomics and metabolomics after liver transplantation and identify biomarkers that can identify liver transplant recipients at high risk of developing cardiovascular, respiratory, renal, and metabolic diseases.

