## Methods/design

The DACOLT study is a non-interventional, observational, longitudinal study to be initiated in March 2021. The study aims to include all liver transplant recipients living in Denmark (n = 580) as well as all patients who will be liver transplanted from 01.03.2021 until 01.03.2033 (estimated n = 600). Controls will be included from the Copenhagen General Population Study (CGPS) and the Copenhagen City Heart Study (CCHS).

Liver transplant recipients and controls will have uniformly measured clinical data and information regarding risk factors. Clinically measured primary outcomes include (1) coronary CT angiography, cardiac structure and function determined by echocardiography and cardiac CT, and electrophysiological abnormalities determined by electrocardiogram (ECG), (2) dynamic lung function indices measured by spirometry, (3) estimated glomerular filtration rates, (4) diabetes and dyslipidaemia. Several other outcomes are measured. Table 1 provides a complete overview of all clinical and physical measurements, Table 2 of biochemical measures, and Table 3 an overview of the content of the questionnaires used in the study.

**Table 1 Tab1:** Clinical measurements and collection of biomaterials

Measurements	Description
Anthropometry	Height: Stadiometer without shoes Weight: Scale (Soehnle, Nassau, Germany) without shoes or heavy clothing Waist and hip circumference: Measuring tape (SECA, Birmingham, UK)
Ankle–brachial-index	Doppler (Sonotrax Basic A, Edan, San Diego, CA, U.S.)
Blood pressure	IntelliVue MP5SC (Philips, Amsterdam, Netherlands)
Electrocardiogram	Cardiosoft V6.73 (GE Healthcare, Buckinghamshire, UK)
Spirometry	EasyOne® ultrasonic spirometer (ndd Medical, Zürich, Switzerland)
eNO	NIOX VERO® (Aerocrine AB, Solna, Sweden)
CT scans	CT angiography, CACS, CT chest, CT upper abdomen. 320-detector MSCT (Canon Aquilion ONE, PRISM, Canon Medical Systems, Otawara, Japan)
Transthoracic echocardiography	Vivid 9 Ultrasound System (GE Healthcare, Horten Norway) M-mode, colour tissue doppler, conventional spectral doppler, 2D speckle tracking, 3-dimensional echocardiography
Biobank	PBMC, plasma, serum

*CACS* coronary artery calcium score, *CT* computed tomography, *MSCT* multi-slice computed tomography, *PBMC* peripheral blood mononuclear cell

**Table 2 Tab2:** Hematological and biochemical measurements

Measurements	Description

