### Planned statistical analyses

Descriptive statistical analyses will be used to assess demographics, risk factors, and physical measurements. Groups will be compared using t-test or Mann–Whitney U test for continuous data and χ2 tests or Fisher’s test for categorical data. The large cohort of controls permits each liver transplant recipients to be matched on age and sex with between 5 and 20 controls. In cross-sectional studies the prevalence of the respective diseases among liver transplant recipients will be compared to the prevalence among the control group using logistic regression adjusted for traditional and/or presumed risk factors. Likewise, numeric variables will be compared using linear regression adjusted for traditional and/or presumed risk factors. For prospective studies, Cox regression, Kaplan–Meier curves, log-rank test, and mixed effect models will be used. In general, missing data is expected to be low and multiple imputations are not likely to be required. Characteristics for loss to follow-up will be assessed.

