There are also limitations to this study. Limitations include selection bias such as healthy volunteer bias, as liver transplant recipients with more severe illness or disability might be less likely to participate. Furthermore, there might be a geographical selection bias, as some of the inclusion (CT scan) takes place in the capital Copenhagen, which may result in people living outside Copenhagen being less likely to participate in this part of the study. Controls from the CGPS and CCHS are included at random, whereas DACOLT participants are included from the outpatient clinics when they are there for routine controls. Exact reason for non-participation will not be recorded, but the number of non-participations will be registered. Since the study is a prospective cohort study there might also be selection bias in participants lost to follow up. As the study collects information on early life events through self-reported questionnaires, there may be some risk of recall bias, albeit this risk is also present for the control groups.

In conclusion, despite improvements of the short-term survival after liver transplant recipients, the long-term survival remains poor, and efforts to improve the long-term survival are needed. This study has the potential to determine prevalence, incidence and risk factors for development of comorbidity in liver transplant recipients and may be used to develop guidelines on screening, monitoring and long-term treatment of liver transplant recipients and thereby improve survival. Use of data will be confined to the study group, but potential collaborators or request for data can be submitted to [contact].

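### Recipients are recruited nationwide but all controls come from greater Copenhagen, so any regional difference left after adjustment is read as a recipient-versus-background difference

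*Protocol article*

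**What the plan says.** Recipients are nationwide. Methods/design states "The study aims to include all liver transplant recipients living in Denmark", and the eligibility section sets no regional limit: "All liver transplant recipient in Denmark aged 18–100 years will be eligible for inclusion in the DACOLT study".

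Controls are regional. The section on controls says "CGPS is an ongoing observational population study with more than 110,000 participants from the greater Copenhagen area" and "CCHS includes a random population sample included from the greater Copenhagen area". No other control source is named.

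Aim 1 (Study objectives) asks "whether the prevalence and incidence of these comorbidities are different from that of the background population".

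Under Planned statistical analyses, each recipient is to be "matched on age and sex with between 5 and 20 controls". The same paragraph plans logistic and linear regression adjusted for established or suspected risk factors. It does not name region of residence.

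The limitations in the Discussion raise geography once, for recipients' uptake of the CT scan: "people living outside Copenhagen being less likely to participate in this part of the study". They do not mention that the controls come from a single area.

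**The concern.** For a recipient who lives outside greater Copenhagen, an age- and sex-matched Copenhagen resident is not drawn from that recipient's own background population. If the prevalence of an outcome differs between regions for reasons the adjustment does not capture, such as environment or access to care, the difference is attributed to being a transplant recipient.

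More controls do not help. They narrow the interval around an estimate whose bias stays the same. Adjusting for region does not work either: outside greater Copenhagen there are recipients but no controls, so a regional effect cannot be separated from recipient status in that stratum.

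The study is powered for a modest prevalence ratio of 1.15 for coronary atherosclerosis, so a modest regional difference could be of similar size to the target effect.

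**Working it through.** **Inputs from the article (Sample size).** 540 recipients, 5,400 controls, alpha 5%. Control prevalence is 50% for coronary atherosclerosis and 11% for ECG changes. Stated power is 0.90 for a prevalence ratio (PR) of 1.15 and 0.82 for a PR of 1.4.

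**Inputs assumed, because the article gives none.** f is the share of recipients living outside greater Copenhagen, 0.50 to 0.70. r is the ratio of outcome prevalence outside versus inside, 1.05, 1.10 or 1.15. There is no true effect of recipient status and no covariate adjustment.

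**Step 1: reproduce the stated power.** Two-sided two-proportion z-test with pooled variance under the null:

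power = Φ[(p1 − p0 − 1.96·SE0) / SE1]

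- Atherosclerosis, 0.575 v 0.50: SE0 = 0.02256, SE1 = 0.02233, power 0.916 (stated 0.90).
- ECG, 0.154 v 0.11: SE0 = 0.01434, SE1 = 0.01611, power 0.838 (stated 0.82).

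Both lie within two percentage points, so the stated power is not in dispute and the same test can be used below.

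**Step 2: spurious PR from region alone.** Only recipients outside the catchment carry the regional ratio:

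spurious PR = 1 + f(r − 1)

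For example, f = 0.50 and r = 1.10 give 1 + 0.50 × 0.10 = 1.05. With f = 0.70 the result is 1.07.

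**Step 3: chance of a significant result with no true effect** (two-sided 5%, both tails counted).

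| r | Spurious PR (f = 0.50 to 0.70) | Atherosclerosis, 50% | ECG, 11% |
|---|---|---|---|
| 1.05 | 1.025 to 1.035 | 9% to 12% | about 6% |
| 1.10 | 1.05 to 1.07 | 20% to 34% | 7% to 9% |
| 1.15 | 1.075 to 1.105 | 38% to 64% | 10% to 14% |

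The nominal rate is 5%. To imitate the full PR of 1.15 with half of the recipients outside, r would have to be 1 + 0.15/0.50 = 1.30.

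**Step 4: precision of an analysis restricted to the catchment.** If 30%, 40% or 50% of the 540 recipients live there (assumption), n = 162, 216 or 270. Against 5,400 controls, power for PR 1.15 in atherosclerosis is 0.47, 0.58 or 0.67.

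**The case against.** The strongest reply is that matching is not the only control for confounding. The article plans adjusted regression. Smoking, education, household income, occupational exposure and alcohol are collected, and the recipients' lifestyle questionnaire is identical to that used in both control cohorts. Much of what makes regions differ could be adjusted away. This stands. A reader might infer from the matching that every regional difference passes straight into the comparison, and the article does not support that. Only the residual difference does.

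A second reply concerns size. A reader might apply the regional ratio to all 540 recipients, which for atherosclerosis gives about 20%, 60% and 92% at ratios of 1.05, 1.10 and 1.15. That assumes no recipient lives in greater Copenhagen, and nothing in the article supports it. The figures in the table are also unadjusted, show one direction only, and rest on an assumed share.

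Third, if distant recipients attend CT less often, as the Discussion expects, the mismatch is smallest for the CT outcomes, where the table shows the largest effect. It would be fuller for ECG, spirometry, eGFR and metabolic outcomes. For ECG the illustrated inflation is small.

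Finally, the control source is openly described, and a covariate list is commonly left to the analysis plan. Both are true, and the exact covariate list is not part of this point. What remains is that covariates cannot stand in fully for region, that no control lives outside the catchment, and that the limitations cover only the recipients' side of geography.

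**Conclusion.** The mismatch is in the text: nationwide recipients, greater-Copenhagen controls, matching on age and sex, and an aim framed against the background population. Adjustment may reduce the resulting bias, but it cannot be shown to remove it.

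The size and direction are unknown. Without adjustment, and with 50–70% of recipients outside the catchment, regional ratios of 1.05 to 1.15 raise the chance of a significant result from 5% to between about 9% and 64% for atherosclerosis, and to between about 6% and 14% for ECG changes. The atherosclerosis figures are an upper range if CT uptake falls with distance.

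This does not show that the comparison is invalid or that an excess in recipients would be false. It is a limitation that should be stated and that a simple analysis can probe.

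**What to change.** 1. Record each recipient's region of residence, for example from patient records, which are already a planned source of transplant-related variables. The article lists vital status, emigration and death as the content of the civil registration system and does not mention residence, so its availability there should be confirmed before it is relied on.
2. Add a sensitivity analysis of each primary recipient-versus-control comparison, restricted to recipients living in the greater Copenhagen catchment and using the same adjusted model as the main analysis. This compares recipients with controls from the same area.
3. In the Discussion, state beside the CT-uptake limitation that all controls come from one metropolitan area.

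The cost is one extra variable, one extra analysis per primary comparison and a sentence of text. No new recruitment is needed. The drawback is precision: with power of about 0.47 to 0.67 for PR 1.15 in atherosclerosis (if 30–50% of recipients live in the catchment), the restricted analysis can only check whether the estimates agree. It should not replace the main analysis, and a non-significant restricted result should not be read as evidence of no difference.

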### Physical and clinical measurements

All data are collected using uniform protocols in the CGPS, CCHS and the DACOLT study (Fig. 1). A physical exam including anthropometrics, pulse, peripheral arterial saturation is performed by trained clinical staff.

#### Blood pressure and ankle–brachial index

Blood pressure is measured electronically on both the right and left arm with the participant in a relaxed seated position using IntelliVue MP5SC (Philips, Amsterdam, Netherlands). Ankle–brachial-index (ABI) is measured in a supine position in both extremities using a Doppler meter (Sonotrax Basic A 294534, Edan, San Diego, CA, US) by determining the systolic pressure of the posterior tibial artery or alternately the pressure of dorsalis pedis artery.

#### ECG

ECG is measured using a 12-lead ECG (Cardiosoft V6.73 GE Healthcare, Buckinghamshire, UK). The ECGs are stored electronically.

#### Spirometry and nitric oxide in exhaled breath

Forced expiratory volume in the first second (FEV1) and forced vital capacity (FVC) are measured by spirometry using an EasyOne World Spirometer (ndd Medical, Zurich, Switzerland) with one-use spirettes (ndd Medical). Spirometry is performed in accordance with American Thoracic Society/European Respiratory guidelines [18]. In participants where the FEV_1_/FVC < 0.7 a repeat spirometry is performed 15 min after bronchodilation with inhalation of 400 µg salbutamol (Ventoline Diskus, Glaxo Smoth Kline, Middlesex, UK). Nitric oxide in exhaled breath (eNO) is measured using NIOX VERO (Aerocrine AB, Solna, Sweden).

### Collection of biomaterials

At time of inclusion blood samples will be collected for routine biochemical analyses (Table 2). A total of 84 ml blood will be collected for a research biobank, and peripheral blood mononuclear cells (PBMC), serum and plasma will be stored for analyses of inflammation markers (chemokines, cytokines, soluble surface markers), coagulation markers (standard and functional platelet aggregation test), simulation assays and flowcytometry of PBMC, endothelial function markers (asymmetric dimethylarginine (ADMA), syndecan-1, thrombomodulin and sE-selectin), markers of microbial translocation and bacterial degradation (sCD14, lipopolysaccharide, trimethylamine N-oxide), markers of lung tissue (alpha-1-antitrypsine, endothelin-1), liver markers (hyaluronic acid and fibrosis markers) and metabolomics and multiomics.

At all follow-up visits, routine blood samples will be drawn and analysed.

### Questionnaires

All participants in DACOLT will complete an extensive questionnaire regarding lifestyle, health, respiratory symptoms and medication, identical to the questionnaire developed and used in the CGPS and CCHS (Table 3). Data based on this questionnaire has been published on several occasions [19–23]. Furthermore, DACOLT participants will also complete a separate questionnaire regarding depression symptoms based on Major Depression Inventory [24] (International Classification of Diseases (ICD)-10) and complete the Fracture Risk Assessment Tool (FRAX®) [25] which is an online algorithm with 12 questions to assess the risk of hip fracture. All these questionnaires will be completed at time of inclusion and at the 10 year follow up. A less extensive questionnaire will be completed at 2-, 4-, 6- and 8-year follow-up.

### CT scans

CT scans will be performed with a 320-detector MSCT (Canon Aquilion ONE, PRISM, Canon Medical Systems, Otawara, Japan) at Rigshospitalet, University of Copenhagen, using identical protocols for DACOLT and GCPS participants. First, in backrest and while holding the inspiration, a high-resolution CT will be performed including all lung parenchyma. Afterwards, CT scan of the heart, liver and abdominal fat will be performed. At last, an intravenous contrast agent (Visipaque 78 ml, 320 mg/ml) will be infused with a flowrate of 5 ml/s followed by a saline chaser and contrast enhanced thoracic and abdominal CT angiography will be performed. The complete CT scan protocol includes several scans performed in the following sequence: Unenhanced CACS, scan of the upper abdomen, abdominal single slice acquisition for measurements of visceral adipose tissue, low-dose chest CT and a contrast enhanced coronary angiography with iodixanol (Visipaque®, GE Healthcare, Brøndby, Denmark). Oral β_1_-antagonist (Metocar, STADA Nordic, Herlev, Denmark) will be administered to patients with a heart rate > 60 bpm and systolic blood pressure > 110 mmHg unless contraindicated. Participants with moderate to severe COPD/asthma will receive Ivabradin 15 mg (Procoralan, Servier, Fredriksberg, Denmark) instead of a β_1_-antagonist. Immediately before CT angiography is performed, one dose of 0.4 mg oral spray nitroglycerin (Nitrolingual, Pohl Boskamp, Hohenlockstedt, Germany) is administered unless contraindicated. The maximum allowed radiation dose for the complete sequence is 8 mSv, and CT will not be performed in patients where the expected radiation dose exceeds 8 mSv.

### Transthoracic echocardiography

Echocardiography will be performed using a pre-specified comprehensive protocol using the Vivid 9 Ultrasound System (GE Healthcare, Horten, Norway). Participants will be examined in the left lateral decubitus position with conventional echocardiography; including M-mode, and colour tissue doppler (TDI), 2D speckle tracking for deformation analyses (strain) as well as 3-dimensional echocardiography. Echocardiograms will be stored in a GE Healthcare image vault, and images will be analysed offline with commercially available post-processing software.

### Other data sources

For DACOLT participants, liver- and transplantation-related variables will be retrieved from patient records. In Denmark, all liver transplant recipients are routinely examined annually with liver biopsies, magnetic resonance imaging (MRI), including MR elastography, and routine blood samples. Furthermore, information on vital status, medicine use and discharge diagnosis can be retrieved from National Danish registries. The Civil Registration System (CRS) contains information on vital status, date of emigration and death of every resident in Denmark [26]. The Danish National Patient Register (NPR) contains information on all hospital admissions to Danish hospitals including discharge diagnoses according to the ICD-10 from 1994 [27]. From the NPR, data on admissions due to cardiovascular, lung, bone, metabolic, and liver diseases will be retrieved. Information regarding purchase and use of medication related to these diseases will be retrieved from the registry of Medicinal Product Statistics that contains information on medicine since 1994, including all prescription and non-prescription drug sales from pharmacies, and all deliveries from general practitioners and hospitals [28].

### Sample size

The current study includes several endpoints, and the necessary sample size varies accordingly.

Previous data from the CGPS have shown coronary atherosclerosis in 50% of the background population [29]. In the following we assume that 90% of the invited liver transplant recipients are included in the study.

Assuming coronary atherosclerosis in 50% of the CGPS participants [29], an alpha of 5%, 540 liver transplant recipients and 5400 controls, we will, with a power (1-β) of 0.90, be able to show a prevalence ratio of 1.15 for atherosclerosis. Assuming ECG changes in 11% of CGPS participants [30], an alpha of 5%, 540 liver transplant recipients and 5,400 controls, we will with a power (1-β) of 0.82 be able to show a prevalence ratio of 1.4 to have ECG abnormalities. In the Danish general population, 1 unit (%) decrease in absolute global longitudinal strain (GLS) is associated with 10% increased risk of heart disease [31]. Assuming an alpha of 1%, a standard deviation of 3.5%, 540 liver transplant recipients and 2,160 controls, we will be able to show a difference of 1% GLS with a power (1-β) of 0.99.

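### Detectable effects for the two binary endpoints are prevalence ratios, but the only adjusted analysis of prevalence is logistic regression, with no stated step to an adjusted prevalence ratio

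*Protocol article*

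**What the plan says.** Aim 1, under Study objectives in the protocol article, is to determine how common each group of comorbidities is in recipients and whether this differs from the background population.

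The Sample size section sizes two binary endpoints for that comparison:

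- Coronary atherosclerosis: "Assuming coronary atherosclerosis in 50% of the CGPS participants", with "an alpha of 5%, 540 liver transplant recipients and 5400 controls" and "with a power (1-β) of 0.90", the study will "be able to show a prevalence ratio of 1.15 for atherosclerosis".
- ECG: "Assuming ECG changes in 11% of CGPS participants", with the same alpha and group sizes, the study will "with a power (1-β) of 0.82 be able to show a prevalence ratio of 1.4 to have ECG abnormalities".

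The third calculation, for global longitudinal strain (GLS), uses a difference in means.

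The Planned statistical analyses section says that, in cross-sectional work, prevalence in recipients will be "compared to the prevalence among the control group using logistic regression adjusted for traditional and/or presumed risk factors". It also lists χ² or Fisher's tests for categorical data, and linear regression for numeric variables. It names no log-binomial or Poisson model, and no standardisation from the logistic model.

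**The concern.** Logistic regression returns an odds ratio. The odds ratio is close to the prevalence ratio only when the outcome is rare in both groups, and an outcome present in half of the controls is far from rare. The sample size section and the adjusted analysis are therefore on different scales.

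Three things are at stake:

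- A reader who sets the reported adjusted odds ratio beside the planned 1.15 compares unlike quantities.
- The gap between the scales depends on how common the outcome is. Adjusted odds ratios for a 50% outcome and an 11% outcome are therefore not comparable as measures of excess prevalence. The study's aim is burden, and its Discussion looks ahead to guidelines on screening and monitoring.
- The odds ratio is non-collapsible: adding a strong predictor to the model can move it even without confounding. The covariate set is described only as traditional and/or presumed risk factors. This is a general property of the measure, and the documents give no figures from which to size it here.

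**Working it through.** **Inputs**, all from the Sample size section: 540 recipients; 5,400 controls; alpha 5%; control prevalence p0 = 0.50 (atherosclerosis) and 0.11 (ECG); prevalence ratios (PR) 1.15 and 1.4. The section does not say whether alpha is one- or two-sided. Two-sided is assumed; for atherosclerosis a one-sided test would give 0.955, further from the stated 0.90.

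**Step 1. Recipient prevalence, p1 = PR × p0.**
- Atherosclerosis: 1.15 × 0.50 = 0.575, a difference of 7.5 percentage points.
- ECG: 1.4 × 0.11 = 0.154, a difference of 4.4 percentage points.

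**Step 2. Reproduce the stated power.** For two independent proportions, power = Φ[(d − 1.96 × SE0) / SE1], where d = p1 − p0, SE0 uses the pooled prevalence and SE1 the two separate prevalences.
- Atherosclerosis: pooled prevalence (540 × 0.575 + 5,400 × 0.50) / 5,940 = 0.507; SE0 = 0.02257; SE1 = 0.02234. (0.075 − 1.96 × 0.02257) / 0.02234 = 1.38, so power is 0.916, or 0.909 with continuity correction. Stated: 0.90.
- ECG: pooled prevalence 0.114; SE0 = 0.01434; SE1 = 0.01611. (0.044 − 1.96 × 0.01434) / 0.01611 = 0.99, so power is 0.838, or 0.822 with continuity correction. Stated: 0.82.

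Both figures reproduce, so the endpoints were sized on the prevalence scale, as the text says.

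**Step 3. The same effects as odds ratios, OR = [p1/(1 − p1)] / [p0/(1 − p0)].**
- Atherosclerosis: (0.575/0.425) / (0.50/0.50) = 1.353.
- ECG: (0.154/0.846) / (0.11/0.89) = 1.473.

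**Step 4. Compare the excesses.** Since OR − 1 = (p1 − p0) / [p0(1 − p1)] and PR − 1 = (p1 − p0) / p0, their ratio is 1/(1 − p1).

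| Endpoint | PR | OR | Excess, PR scale | Excess, OR scale | Factor |
|---|---|---|---|---|---|
| Atherosclerosis | 1.15 | 1.353 | 15% | 35% | 1/0.425 = 2.35 |
| ECG changes | 1.40 | 1.473 | 40% | 47% | 1/0.846 = 1.18 |

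The factor exceeds 2 whenever more than half of the recipients have the outcome. With 50% in controls, that means any excess at all: it is 2.11 at PR 1.05 and 2.50 at PR 1.20.

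**Step 5. Power of the unadjusted logistic comparison at the same prevalences** (Wald test of the log odds ratio). SE = √[1/(540 × p1(1 − p1)) + 1/(5,400 × p0(1 − p0))].
- Atherosclerosis: ln 1.353 = 0.302; SE = 0.0912; 0.302/0.0912 − 1.96 = 1.35, so power is 0.912.
- ECG: ln 1.473 = 0.387; SE = 0.1269; 0.387/0.1269 − 1.96 = 1.09, so power is 0.862.

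The change of scale costs no power.

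**The case against.** The strongest case on the other side has four parts.

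- **The matching test is in the plan.** The power calculation is an unadjusted comparison of two proportions, and the χ² test listed under Planned statistical analyses corresponds to it. The crude prevalence ratio is the quotient of the two prevalences that Aim 1 requires. This stands: a reader might infer that the plan never estimates the quantity it was sized for, and that goes too far. What is missing is a stated route to the *adjusted* ratio.
- **Power is intact.** This stands in full. A reader might take 1.15 as the odds ratio the model must detect. That would mean 53.5% against 50%, a prevalence ratio of 1.07 and power of about 0.34. The document says prevalence ratio explicitly, so 0.34 is not a consequence of the plan.
- **An odds ratio labelled as such overstates nothing.** This also stands. The article does not say that an odds ratio will be read as a prevalence ratio, so a claim that the burden will be overstated is unsupported. It is overstated only if the odds ratio is read that way.
- **Logistic regression can yield a prevalence ratio by standardisation, and a condensed article may leave that to the analysis plan.** This is partly right: the two sections do not strictly contradict each other. But the article does fix both a scale for the effect and a model for the adjusted comparison, and the model's direct output is not on that scale. Naming a better-suited estimate improves a choice already made; it is more than a request for detail.

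**Conclusion.** The point holds as a mismatch of effect measure in the adjusted analysis of the two binary endpoints. At the planned effects, prevalence ratios of 1.15 and 1.4 correspond to odds ratios of about 1.35 and 1.47. The gap is large for atherosclerosis (35% against 15%) and modest for ECG changes (47% against 40%).

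It is not an error in the sample size. Power at the planned prevalences is about 0.91 for atherosclerosis and 0.84 to 0.86 for ECG changes, on either scale. The GLS endpoint, a mean difference that the plan would analyse by linear regression, is not concerned.

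The figures rest on the article's own control prevalences, a two-sided 5% test, and an unadjusted, unmatched comparison. An adjusted odds ratio could differ from these values in either direction, depending on the covariates.

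**What to change.** In Planned statistical analyses, name the adjusted prevalence ratio and the adjusted prevalence difference as the primary estimates for cross-sectional binary outcomes. Either of two routes serves:

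- the logistic model already planned, followed by marginal standardisation; or
- modified Poisson regression (log link) with robust variance for the ratio, with the difference obtained by standardisation from the same model.

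In both, the variance should account for the matched sets. Keep odds ratios as supplementary results, labelled as such.

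If the odds ratio is to stay primary, the minimum is to restate the detectable effects in the Sample size section as odds ratios of about 1.35 and 1.47, next to the prevalence ratios.

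The cost is a sentence or two of text and slightly more analysis work in standard software. No new data, participants or change to the sample size are needed.
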